## Abstract

**Background:**

Brucellosis is a common zoonotic disease and a significant public health concern. Effective health management is essential for improving the self-management behaviors of brucellosis patients. This study aims to assess the effectiveness of a mobile health (mHealth) intervention based on the Health Action Process Approach (HAPA) model in enhancing self-management among brucellosis patients.

**Methods:**

This single-center, single-blind randomized controlled trial will be conducted at the Fourth Central Hospital of Baoding City, Hebei Province, China (ChiCTR2300071152). A total of 58 participants will be randomly assigned to the mHealth intervention group or the routine education group. Inclusion criteria: (1) Aged ≥18 years, (2) Diagnosed with brucellosis, (3) Familiar with WeChat, (4) Voluntary consent. Exclusion criteria include severe comorbidities, psychotropic medication use, and pregnancy. The intervention will be delivered via WeChat, using educational materials such as articles, videos, and case studies. The control group will receive standard discharge education. Primary outcomes include health behavior formation and health literacy, and secondary outcomes include psychological variables and behavior change. Statistical analyses will be conducted using SPSS Statistics 26.0. Data will be expressed as mean ± standard deviation or count (%). Parametric or non-parametric tests will be used as appropriate, and missing data will be handled using multiple imputation methods. A *p*-value <0.05 will be considered statistically significant.

**Discussion:**

This study will contribute to understanding the application of the HAPA model in guiding health interventions for brucellosis patients. It will be the first study in China to apply the HAPA model in this context, providing insights into its effectiveness for improving health behaviors and long-term outcomes in brucellosis patients.

## Introduction

1

Brucella is a widespread zoonotic infection globally (1, 2). According to the World Health Organization (WHO), Brucella is defined as a disease that can be naturally transmitted from vertebrates to humans (3). It primarily originates from infected or severely infected animals, such as cows and sheep (4, 5). The main transmission routes include the digestive tract, skin, mucous membranes, and respiratory tract, through contact with blood, body fluids, and aerosols. The disease typically manifests with high fever, excessive sweating, malaise, and arthralgia, and can be more severe in some cases (6, 7). Brucella was first reported in China in 1905. In recent years, however, the prevalence of brucellosis has significantly increased (8, 9). National surveillance data reveal that, with the increase in livestock farming in China in recent years, the incidence rate of human brucellosis has shown a sustained upward trend in some regions. From 2004 to 2014, the national incidence rate rose from 0.92 to 4.2 cases per 100,000 people, and between 2004 and 2021, it increased by a total of 8.20%, seriously affecting both livestock production and public health (10–12).

The impact of brucellosis is twofold: it not only affects livestock production, causing substantial economic losses, especially in rural areas of developing countries where livestock farming is the primary economic activity (13–15), but also poses serious threats to human health and safety. One of the most effective ways to manage brucellosis is through public education on preventive behaviors, particularly for at-risk groups (15, 16). Health management strategies play a crucial role in controlling brucellosis (17). Therefore, educating individuals and changing their behaviors and lifestyles to prevent the disease is regarded as the best and most practical approach to controlling brucellosis.

Diagnosis and treatment after infection have limited effectiveness in controlling the disease. With advancements in medical technology, there is a growing demand for personalized and precise disease management for brucellosis patients. However, due to limitations in manpower and resources, primary healthcare organizations and medical staff often provide inadequate intervention management for brucellosis patients. Therefore, innovative mHealth interventions are essential for enhancing the management of brucellosis patients (18).

Mobile health, or mHealth, refers to the use of mobile devices, such as smartphones, patient monitoring devices, and wireless devices, to provide medical support and manage patient health (19). The rapid development of mobile networks has resulted in the widespread use of mobile electronic devices. A 2015 report indicated that more than seven billion mobile device subscriptions exist worldwide (20). This proliferation has made mHealth feasible, widespread, and replicable, utilizing features such as text messaging, email, phone calls, and mobile applications (21–24). One of the advantages of mHealth is that it requires no additional resources for implementation (25). The cost of monitoring clinical data and communicating educational information between doctors and patients is lower than that of face-to-face services (25). Furthermore, mHealth overcomes geographical barriers, enhances accessibility, and delivers health services to remote and underserved areas (26). By incorporating multimedia and big data, mHealth applications can enhance the health behaviors of individuals using these technologies (27, 28). MHealth lies at the intersection of communication technologies and personalized healthcare (29).

In the field of infectious disease management, mHealth interventions have shown significant potential. For instance, studies have shown that mHealth interventions, such as text message reminders and health information push notifications through social media platforms, can significantly improve adherence to antiretroviral therapy and improve patients’ mental health (30). Similar interventions have also been successful in tuberculosis management, particularly in enhancing patients’ self-management capabilities and treatment completion rates (31). These studies indicate that mHealth plays a critical role in improving health behaviors and self-management, especially in resource-poor regions and populations. However, mHealth-based interventions alone may lack theoretical guidance, potentially limiting the effectiveness of the intervention. Previous studies have emphasized that the design of mHealth interventions should be based on one or more theoretical models or frameworks to ensure their effectiveness and sustainability (32, 33).

The Health Action Process Approach (HAPA), shown in Figure 1 and developed by Litt et al. (34), suggests that health behavior change involves a series of psychological factors. It proposes that behavior change progresses through different stages, facilitating the effective transition from behavioral intentions to external behaviors. The HAPA model integrates relevant variables from the continuum model and stage theory model. It incorporates intrinsic motivational and volitional factors, such as self-efficacy, risk perception, and outcome expectancy (35), as well as behavioral intentions and action plans (36). It also considers extrinsic behavioral activities, such as inaction, irregularity, and regularity, as well as macro-environmental factors that affect the formation of intentions, initiation of actions, and maintenance of behaviors. By classifying individuals into different groups based on their motivational, volitional, and behavioral factors, the HAPA model links behavioral intentions to health behaviors through the use of implementation intentions, such as action plans, coping plans, self-monitoring, and self-regulation, thereby promoting the effective transition from intentions to behaviors (37). HAPA-based interventions have been proven effective in promoting health behavior changes (38–42). Specifically, the HAPA model has been applied to the study of COVID-19-related health behaviors during the pandemic, where the motivational and volitional factors included in HAPA increased adherence to protocols such as wearing masks and handwashing (43, 44). Additionally, the HAPA model has been used to assess social distancing behaviors during the pandemic, further emphasizing its applicability (45). In managing chronic diseases, a HAPA-based study in Iran demonstrated that the seven structures of HAPA were effective in promoting a healthy diet in patients with type 2 diabetes (46).

**Figure 1 fig1:**
[figure not shown]
Schematic diagram of health action process approach.

To date, no research has focused on the application of the HAPA model in the health management of brucellosis patients. Therefore, applying the HAPA model in the health management of brucellosis patients could significantly contribute to improving their health behaviors.

This study aims to develop a health education intervention model for brucellosis patients based on the HAPA framework. The first step involves assessing the current level of knowledge regarding brucellosis among patients. Drawing from best practice evidence, brucellosis-related information will be integrated to design a personalized health management intervention program for patients. The intervention will be delivered through the WeChat platform and mobile health devices, utilizing doctor-patient interaction for interactive health education. The goal is to deliver lifestyle-based behavioral interventions to assist patients in developing self-management habits.

The intervention tested in this trial will be based on the Health Action Process Approach (HAPA) model, which incorporates behavior change processes such as self-efficacy, risk perception, and the formation of action plans. This theoretical framework will guide the development and delivery of mHealth-based interventions, ensuring that the intervention is rooted in behavioral science to improve health outcomes in brucellosis patients. By integrating multimedia content and offering continuous support through mobile health devices, the intervention aims to enhance patient engagement and improve long-term self-management behaviors. The control group will receive usual care, which does not include mHealth interventions based on behavior change models. Usual care for brucellosis patients typically involves standard medical treatment, such as general health education, but lacks structured mHealth behavioral interventions. The choice of usual care as the comparator is justified by the absence of structured mHealth behavioral interventions for brucellosis. Since no established mHealth interventions are available for brucellosis, the comparison with usual care, which does not include a behavior change intervention, is the most appropriate to evaluate the effectiveness of the proposed intervention.

A rational research design will be used to analyze the impact of mobile health devices on the behavioral changes of brucellosis patients and the underlying mechanisms. This study aims to provide a clinical basis for the treatment plan, prognosis, and rehabilitation of brucellosis patients, serving as an initial step toward the broader implementation of mobile health interventions. Furthermore, the findings of this intervention may inform policy recommendations and guide technical transformations in the development of mobile health management applications.

The specific research objectives of this study include the following:

(1) To develop and evaluate an mHealth-based intervention model, integrating the HAPA model, aimed at improving health behaviors and enhancing self-management in brucellosis patients.(2) To compare the effectiveness of the HAPA-based mHealth intervention with traditional management models, hypothesizing that the mHealth intervention will more effectively improve health behaviors and enhance self-management.

## Methods

2

### Study design

2.1

The study is an intervention randomized controlled trial in Baoding No. 4 Central Hospital, Hebei Province. The study employs quantitative research methods, using questionnaires based on brucellosis-related knowledge and internationally recognized scales for measurement. This approach ensures the objectivity of the study. The study will be conducted from December 2024 to December 2025. The intervention will last for 3 months, followed by a 12-month follow-up phase for data collection and evaluation. The questionnaire was given at the beginning then every 3 months which was then analyzed. The control group will receive conventional education, while the experimental group will receive mHealth education. The study aims to compare the effectiveness of mHealth interventions on the health behaviors of brucellosis patients based on the HAPA model, hypothesizing that mHealth interventions are more effective than conventional interventions (43). The flow chart of the study is shown in Figure 2 and Table 1.

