**Figure 2 fig2:**
[figure not shown]
Flow chart of patient recruitment and study implement.

**Table 1 tab1:** Timeline for study enrollment, intervention, and evaluation.

	Study period						
	Recruitment	Allocation	Intervention		Follow-up		
Timepoint	-T1	0	Month 0	Month 3	Month 6	Month 9	Month 12
Enrollment							
Informed consent	√						
Eligibility screen	√						
Allocation		√					
Intervention							
HAPA-mHealth							
Control							
Assessments							
Sociodemographic variables			√				
Proportion of individuals adopting health behaviors			√	√	√	√	√
Knowing rate of health knowledge			√	√	√	√	√
Refill and medication adherence scales			√	√	√	√	√
Quality of life			√	√	√	√	√
Depression and anxiety			√	√	√	√	√
Perceived stress scale			√	√	√	√	√
Perceived social support			√	√	√	√	√
Satisfaction				√	√	√	√

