### Study setting, randomization and blinding

2.2

The study will be a single-center, single-blind randomized controlled trial conducted at the Fourth Central Hospital of Baoding City, Hebei Province. Convenience sampling will be employed to recruit patients diagnosed with brucellosis. In this study, patient enrollment was conducted in batches to ensure feasibility, sample balance, and control of potential confounding factors. Specifically, eligible patients were enrolled in batches based on established time points, screening criteria, and enrollment procedures to ensure the study’s orderly and efficient progress.

Randomization was performed using Excel software to ensure unbiased group allocation. A new worksheet was created with numbers 1 to *N* in column A, where *N* represents the total number of participants. In column B, the formula = RAND() was used to generate random numbers between 0 and 1 for each participant. These random numbers were then fixed by copying and pasting them as ‘values’ to prevent modifications. The participants were then sorted by their random numbers in ascending order, and group assignments were made accordingly. The random allocation sequence will be generated by the researchers.

A single-blind design was implemented to ensure blinding. Participants were blinded to their group allocation, while evaluators remained aware of the group assignments. Allocation concealment was achieved using the envelope method. Adequate opaque envelopes were prepared, each labeled with a unique identifier number. A small slip of paper containing group assignment information was placed inside each envelope and sealed. After enrollment, participants received envelopes in sequential order based on their numerical identifiers and opened them independently to reveal their group assignment. The distribution and opening of envelopes were supervised by a designated individual to ensure the integrity of allocation concealment, and the process was documented for transparency. Unused envelopes were securely stored to preserve allocation concealment and maintain the single-blind design.

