### Study participants

2.3

The study was approved by the Ethics Committee of Baoding No. 4 Central Hospital. Participants will be patients from Baoding No. 4 Central Hospital, located in Baoding City, Hebei Province, China. Recruitment of study participants is expected to begin in December 2024. After enrolling in the trial and signing the informed consent form through face-to-face communication at the hospital, each participant will begin the formal trial intervention. Therefore, participants will be recruited and begin the intervention at different times. They will all complete the 3-month intervention cycle.

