
This study investigated the effectiveness of the mHealth intervention by comparing the experimental group with HAPA as the guiding theory of mHealth to the control group with routine discharge education. In future studies, it should also be compared with mHealth that is not based on the intervention theory. This comparison can provide insights into the impact of the theory-based approach on the effectiveness of the mHealth intervention.

The planned study, which aims to enroll 58 participants, serves as an initial exploratory investigation. However, its small sample size limits its ability to represent the full spectrum of brucellosis patients, particularly with regard to geographical, age, gender, and disease severity diversity. The study is further limited by being conducted at a single center, which raises concerns about the generalizability of the findings to other regions, particularly rural and underserved areas with differing healthcare access. Another limitation is the potential bias inherent in self-reported data, which may affect the accuracy of participants’ reported health behaviors and self-management practices, potentially introducing social desirability or recall bias. Furthermore, although a 12-month follow-up is planned, the long-term impact of the intervention remains uncertain, raising the crucial question of its durability and patients’ sustained adherence. The use of the WeChat platform for the mobile health intervention, although widespread in China, presents challenges as not all patients are familiar with or inclined to use this medium. Additionally, individual preferences for receiving health information vary, highlighting the need for further consideration in the study’s design and execution.

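### The December 2024 to December 2025 study window cannot hold the 15 months per patient in section 2.1, and holds Table 1's 12 months only for patients enrolled in December 2024

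*Protocol article*

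**What the plan says.** Four parts of the protocol article bear on the calendar.

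- **Section 2.1 (Study design), dates:** "The study will be conducted from December 2024 to December 2025".
- **Section 2.1, duration per patient:** "The intervention will last for 3 months, followed by a 12-month follow-up phase for data collection and evaluation". Questionnaires are given at the start and every 3 months.
- **Table 1** ("Timeline for study enrollment, intervention, and evaluation"): intervention columns at Months 0 and 3, follow-up columns at Months 6, 9 and 12. There is no later column.
- **Sections 2.2 and 2.3, entry:** "Recruitment of study participants is expected to begin in December 2024", and "participants will be recruited and begin the intervention at different times". Section 2.2 adds that "eligible patients were enrolled in batches based on established time points".

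The Discussion says "although a 12-month follow-up is planned" without saying from which point the 12 months are counted. No recruitment closing date or recruitment length is given, and nothing says that follow-up continues after December 2025.

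**The concern.** Neighbouring sentences in section 2.1 cannot both be carried out. The stated dates are too short for the stated duration even for the first patient. Table 1 gives a different and shorter duration, which still leaves almost no time to recruit.

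If the dates were followed, patients who enter later would lose their late visits because the study closes. That is administrative missingness. It is separate from the dropout for which section 2.4 allows 20%.

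Three things depend on the late visits:

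- the per-protocol set in section 2.9, which requires both intervention and follow-up to be completed;
- the longitudinal analysis across time points promised in the Discussion;
- any statement about effects at 12 months.

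Section 2.9 also compares baseline with an endpoint that it does not date. The main comparison would be affected too if that endpoint were meant to be the last visit.

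**Working it through.** **Inputs.** Window: December 2024 to December 2025 (section 2.1). Duration per patient: 3 + 12 months (section 2.1 text) or 12 months from Month 0 (Table 1). Start of recruitment: December 2024 (section 2.3). Sample: 58 patients, 20% loss allowance (section 2.4). Recruitment length R: not stated, so it is an assumption and is varied below.

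**Step 1: the window, W.** The longest reading, 1 December 2024 to 31 December 2025, is 395 days; 395 / 30.4375 = 12.98 months. The shortest, 31 December 2024 to 1 December 2025, is 335 days; 335 / 30.4375 = 11.0 months. The longest reading is used from here on, as the most favourable to the plan.

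**Step 2: the text schedule.** 3 + 12 = 15 months, and 15 − 12.98 = 2.02 months too long. A patient enrolled on 1 December 2024 would finish on 1 March 2026. The number able to finish inside the window is 0 of 58, whatever the accrual.

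**Step 3: the Table 1 schedule.** 12.98 − 12 = 0.98 month is left for recruitment. Only patients enrolled in December 2024 can reach Month 12. On the shortest reading of the window, none can.

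**Step 4: share reaching each visit under Table 1.** With uniform accrual over R months from 1 December 2024, the share able to reach visit v is (12.98 − v) / R, capped at 0 and 1. For example, Month 12 with R = 3 gives 0.98 / 3 = 33%.

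| R (months, assumed) | Month 3 | Month 6 | Month 9 | Month 12 | Month 12, of 58 |
|---|---|---|---|---|---|
| 1 | 100% | 100% | 100% | 98% | 57 |
| 2 | 100% | 100% | 100% | 49% | 28 |
| 3 | 100% | 100% | 100% | 33% | 19 |
| 6 | 100% | 100% | 66% | 16% | 9 |
| 9 | 100% | 78% | 44% | 11% | 6 |

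Rounding the window to 13 months changes little: for R = 6, Month 12 becomes 1 / 6 = 17% and Month 9 becomes 4 / 6 = 67%.

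**Step 5: thresholds.** More than 20% miss Month 12 when 0.98 / R < 0.80, that is R > 1.2 months. More than half miss it when 0.98 / R < 0.50, that is R > 1.95 months.

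**Step 6: against the planned sample.** Section 2.4 needs 23 per group, 46 in all, and 23 / 0.80 = 28.75, rounded up to 29 per group, gives its 58. With R = 3, about 19 patients could have a Month 12 value, before any ordinary dropout.

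**The case against.** The strongest reply is that this is loose wording with a conditional consequence. Table 1 is the explicit assessment schedule and has no Month 15, and the Discussion's 12-month follow-up is compatible with it. The 15-month figure rests on one sentence. Nothing says that visits stop or that data are locked in December 2025, and section 2.6 plans for complete follow-up. The likelier outcome of a short calendar line is that the end date slips.

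Much of this stands, and it limits the point in three ways.

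- **A reader might infer that most patients cannot reach the last visit.** Under Table 1 the article does not establish that. With 1 month of accrual about 98% reach Month 12. The inference needs accrual longer than about 2 months, and the recruitment length is not given. Recruiting nearly everyone in December 2024 does, however, sit awkwardly with batches and differing start times.
- **A reader might infer that the primary comparison fails.** Section 2.9 does not date its endpoint, and Month 3, the end of the intervention, stays reachable for all patients in the scenarios tabulated. Month 6 does too with accrual up to 6 months.
- **A reader might infer bias between the arms.** Nothing here shows it. Loss fixed by entry date would tend to strike both randomised arms alike, so the main cost is precision at late visits.

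What does not stand is treating the conflict as harmless. Even if Table 1 is the intended schedule, the stated dates allow less than one month of recruitment. Nor is this detail left to a fuller document, since the article itself states figures that are incompatible.

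**Conclusion.** The point holds as an internal contradiction. Against the text schedule it is absolute: 15 months do not fit into at most 13, for any patient and under any accrual. Read literally and kept to the dates, the per-protocol set would be empty.

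Against Table 1 it is conditional. Only December 2024 enrollees can reach Month 12, and the share this represents runs from about 98% to 11% as accrual goes from 1 to 9 months. Those shares assume uniform accrual from 1 December 2024, closure on 31 December 2025 and no other loss. A later start or an earlier closing day within those months lowers them.

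The exposure is confined to the late visits and the analyses that need them. It extends to the primary comparison only if the endpoint in section 2.9 is one of those visits.

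**What to change.** Amend section 2.1 so that it agrees with Table 1 and section 2.3.

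1. State whether the last assessment falls 12 months after baseline, as in Table 1, or 12 months after the end of the intervention. The article does not settle which was meant. If the latter, Table 1 needs a Month 15 column. Use the same origin in the Discussion.
2. State a closing date for recruitment.
3. Replace the fixed December 2025 end with the date of the last randomised patient's final scheduled assessment. That falls R + 12 or R + 15 months after the start. With an assumed 6 months of recruitment, this is 18 or 21 months, about June or September 2026.
4. If the end date cannot move, state which late visits will be incomplete by design, and do not claim 12-month results for the full sample.

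The cost is an amendment to the dates and to the follow-up sentence, plus a later final report. No extra patients are needed.
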